## Abstract

**Background:**

Obesity is a growing public health issue associated with comorbidities and substantial medical costs. Although bariatric and metabolic surgery (BMS) is often recommended for individuals with severe obesity, prehabilitation may optimize their physical and psychological status. However, face-to-face delivery can limit accessibility, and evidence on home-based approaches remains scarce.

**Objective:**

This study protocol aims to compare the effectiveness of a home-based prehabilitation program with a face-to-face prehabilitation program on physical and psychological variables in individuals with severe obesity awaiting BMS.

**Methods:**

This is a study protocol for a randomized, controlled, parallel-group trial. To ensure ecological validity, recruitment will be stratified to target 50% low-income and 20% rural participants. Participants with grade III obesity and an indication for BMS will be allocated via block randomization to 3 groups (1:1:1): a face-to-face group, a home-based group, and a control group. The intervention will last 7 weeks (1 week of familiarization plus 6 weeks of training) and will include 12 combined aerobic and resistance exercise sessions and 3 health education sessions. The primary outcome will be the total score of the Hospital Anxiety and Depression Scale (HADS). Secondary outcomes include the HADS subscales (HADS-A and HADS-D), sleep quality, mood states, self-efficacy, quality of life, and functional performance (6-minute walk test, handgrip strength, and 5-repetition sit-to-stand test).

**Results:**

This study was funded in August 2025 by the Research Support Program of the Santa Catarina State University. Recruitment is scheduled to begin in April 2026. The intervention phase is expected to be completed in September 2026, followed by data analysis between October and November 2026. Results are expected to be published in mid-2027.

**Conclusions:**

This trial will provide evidence on the comparative effectiveness of home-based and face-to-face prehabilitation for individuals with severe obesity. The findings can be used to support the implementation of feasible, accessible, equitable, and cost-effective preoperative care models.

## Introduction

Obesity is a health condition that has grown significantly over the past 50 years [1], affecting approximately 2 billion adults [2]. It is estimated that one-third of the global population is overweight or obese [1], which represents a major public health problem due to its association with multiple diseases [3-5].

Obesity is characterized by the excessive accumulation of adipose tissue and is recognized when the BMI is ≥30 kg/m^2^. Severe obesity is classified when the BMI is ≥40 kg/m^2^ or at least 35 kg/m^2^ with associated comorbidities [6]. Recently, a new classification has been proposed that distinguishes “preclinical obesity,” marked by excess fat without functional impairment, from “clinical obesity,” characterized by organ and tissue damage. This framework suggests associating BMI with additional indicators, such as waist circumference and body composition, for a more precise assessment of health status [7].

Obesity is often associated with excessive calorie consumption and low levels of physical activity (PA), leading to an energy surplus [8,9]. However, genetic and environmental factors are also responsible for weight gain [2]. In addition, obesity is associated with several comorbidities, including diabetes mellitus, dyslipidemia, and hypertension [3]; cardiovascular diseases; obstructive sleep apnea and chronic obstructive pulmonary disease (COPD) [5,10]; cancer [4]; morbidity and mortality from chronic diseases; and premature death [10,11]. Other disorders, such as depression and anxiety, are also linked to obesity, sometimes as contributing factors and, in other cases, as consequences of stigma and discrimination, negatively affecting mental health [8,12].

It is estimated that people with obesity incur 30% higher health care costs than those with a BMI within the range considered healthy [1]. In Brazil, data from the Brazilian Association for the Study of Obesity and Metabolic Syndrome show that people with obesity spend 15% of their income on health care treatments, rising to 30% in severe cases. This economic impact underscores the need for studies that explore effective treatment strategies to support both patients and health care systems.

Although exercise, diet, and psychological support are recommended for the management of obesity, these strategies are complicated for individuals with severe obesity to follow, due to mobility limitations, exercise barriers, and difficulties in preparing meals [13,14]. Thus, in many cases, bariatric and metabolic surgery (BMS) is indicated [15,16].

BMS procedures alter the gastrointestinal tract to decrease calorie intake or absorption [16]. Despite being relatively safe, all surgical procedures carry risks, including complications and adverse outcomes. Postoperative complications occur in approximately 30% of major abdominal surgeries [17,18]. Because obesity is itself a surgical risk factor, patients must be adequately prepared to cope with the physiological stress of surgery. In this context, prehabilitation programs have been proven to be fundamental in improving surgical outcomes [12,15,19].

Despite the importance of prehabilitation, its implementation remains inconsistent, and low adherence reduces program effectiveness. To address this inadequacy, several studies have explored remote prehabilitation strategies [20]. Home-based intervention programs have grown in recent years, especially since the COVID-19 pandemic [20-22], and research has been conducted to test the effects of these programs in populations with fibromyalgia [22], older adults [23], and patients with heart disease [24]. Psychological aspects are important in the prehabilitation process, influencing participation and outcomes. It is also known that physical exercise can promote positive results in variables such as sleep [25,26], mood [27,28], quality of life [29,30], and depression and anxiety [31,32]. However, there is still a lack of prehabilitation studies specifically designed for individuals with obesity awaiting BMS. Comparative trials of home-based vs face-to-face programs are particularly scarce.

Home-based prehabilitation supported by digital technologies can empower patients to take an active role in preparing for surgery and managing their health [33]. Digital health intervention programs can help overcome geographical barriers and enhance access to care for patients, health care professionals, and health care systems. These tools have been evaluated as strategies to deliver surgery-related education, support self-monitoring and goal-setting, provide reliable information, and increase preoperative and postoperative engagement [34].

In BMS prehabilitation, health education is often integrated with exercise, offering individualized follow-up and identification of barriers, teaching of behavioral strategies, goal setting, and guidance in the practical application of exercises [35]. Sessions typically address nutrition, PA, behavioral modification, and obesity-related knowledge, thereby supporting lifestyle change and patient engagement [36].

Despite these advances, direct comparisons between home-based and face-to-face prehabilitation programs that integrate PA measures with mental health outcomes are limited. Therefore, this protocol study aims to compare the effectiveness of a home-based prehabilitation program and a face-to-face prehabilitation program on physical and psychological variables in individuals with severe obesity awaiting BMS. Thus, this study aims to address this gap by evaluating the effectiveness and feasibility of a structured 7-week, exercise-based prehabilitation program for individuals with severe obesity awaiting BMS.

## Methods

### Study Design

This is a study protocol for a randomized, controlled, parallel-group trial, developed in accordance with the SPIRIT (Standard Protocol Items: Recommendations for Interventional Trials) guidelines (Checklist 1) [37]. Table 1 presents the schedule of enrollment, interventions, and assessments.

**Table 1. T1:** SPIRIT (Standard Protocol Items: Recommendations for Interventional Trials) 2025 schedule of enrollment, interventions, and assessments for the randomized controlled trial. Adapted according to the SPIRIT 2025 statement.

	Enrollment	Study period				
		Allocation	Postallocation			
Timepoint	–T1	0	T1 (baseline)	Familiarization	T2 (intervention)	Follow-up
Enrollment						
Eligibility screen	✓					
Informed consent	✓					
Allocation		✓				
Interventions						
Combined exercise face-to-face				✓	✓	
Home-based combined exercise				✓	✓	
Control				✓	✓	
Assessments						
Anthropometric measurements			✓			✓
Sit-to-stand test			✓			✓
Handgrip strength			✓			✓
6-minute walk test			✓			✓
Physical Exercise Self-Efficacy Scale			✓			✓
World Health Organization Quality of Life–BREF			✓			✓
Brunel Mood Scale			✓			✓
Pittsburgh Sleep Quality Index			✓			✓
Hospital Anxiety and Depression Scale			✓			✓

### Ethical Considerations

The study was approved by the Research Ethics Committee of the Santa Catarina State University (UDESC), Brazil (CAAE 88170725.1.0000.0118) and registered in the Brazilian Clinical Trials Registry (ReBEC; registration: RBR-59xgczn). All participants will provide written informed consent. Although blinding of participants and providers is not feasible due to the nature of the interventions, outcome assessments will be performed by independent evaluators blinded to group allocation, with interrater reliability established in pilot assessments conducted in 2025 (intraclass correlation coefficient=0.95). Statistical analyses will be conducted by a blinded statistician, with group codes disclosed only after completion of the primary analyses.

### Participants

Recruitment will occur through dissemination via social media, institutional websites, hospitals, primary health care units, and medical clinics. To mitigate selection biases and promote equity in access to research, the sampling design provides stratified recruitment: 50% of the sample will consist of low-income individuals, and 20% will be residents of rural areas. Verification of these demographic characteristics will occur during the initial telephone contact, at which time the objectives, risks, and benefits of the study will also be presented to potential participants. This will be followed by an initial interview to obtain informed consent and initiate data collection. Data collection will take place at the UDESC, in the Health and Sports Science Center.

Participants will be randomized to 1 of 3 groups: a face-to-face exercise group (FxF), a home-based exercise group (HBG), or a control group (CG) (Figure 1).

**Figure 1. F1:**
[figure not shown]
Flow diagram of the study participants according to the CONSORT (Consolidated Standards of Reporting Trials).

### Eligibility Criteria

Individuals of both genders with grade III (severe) obesity who meet the following criteria will be included in the research: (1) BMI>40 kg/m^2^, (2) indication for BMS, (3) formal indication for preoperative physical therapy signed by the BMS surgeon, in accordance with the multidisciplinary guidelines for BMS, (4) absence of comorbidities that compromise safety or the ability to perform the exercises and functional tests, and (5) no participation in any structured exercise program in the past 3 months. To ensure equitable access and diversity, recruitment will be stratified to achieve a sample composition of 50% low-income individuals (defined as monthly household income per capita ≤0.5 minimum wage or total household income ≤3 minimum wages) and 20% residents of rural areas. In addition, participants will be excluded if they meet any of the following criteria: (1) presence of a pacemaker, history of myocardial infarction within the previous 3 months, or unstable angina pectoris; (2) sustained or episodic cardiac arrhythmias aggravated by PA, symptomatic peripheral vascular disease, or any clinical condition representing a risk (eg, inability to safely tolerate heart rate increases >20 beats/min during exercise); (3) clinical diagnosis of acute or chronic respiratory diseases that compromise the safety of physical tests (eg, COPD and asthma with remodeling) or peripheral oxygen saturation (SpO₂) <92% during the 6-minute walk test (6MWT); (4) history of previous BMS or abdominal or thoracic surgery within the previous year; (5) abusive use of or chemical dependence on psychoactive substances (including alcohol and illicit drugs), according to clinical criteria or previous diagnosis; (6) cognitive or physical changes that prevent performance of the tests; and (7) initiation of another form of physical training during the intervention period.

### Randomization and Blinding

After the initial assessment, participants will be allocated through block randomization to receive different interventions performed by physical education professionals and physiotherapists. Participants will be randomly assigned in a 1:1:1 ratio to the HBG, FxF, or CG groups. The randomization sequence will be computer-generated using Sealed Envelope [38], with fixed block sizes of 6 to ensure balanced group allocation throughout recruitment.

Allocation concealment will be ensured using sequentially numbered, opaque, sealed envelopes prepared by an independent researcher who is not involved in recruitment, assessment, or intervention delivery. Envelopes will be opened only after the completion of baseline assessments, minimizing the risk of allocation prediction and selection bias.

The researcher responsible for recruitment, eligibility, and evaluation, as well as statistical analysis, will be unaware of the group to which the individual belongs (blinding of the evaluator and statistician). Due to the type of research, it will not be possible to blind the physical education professionals and physiotherapists responsible for the intervention. Stratification applies only to the recruitment process and not to the randomization procedure.

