#### Face-to-Face Program

Two researchers with experience in interventions for individuals with obesity will conduct the training sessions at the physiotherapy clinic at UDESC. The sessions will be held in the afternoon and last approximately 70 minutes. The first week will be dedicated to familiarizing participants with the exercise protocol.

Initially, participants will perform 30 minutes of aerobic exercise (treadmill or stationary bike). Once this stage is complete, they will begin a protocol of strength exercises, which will include arm flexion (incline), cable row, and shoulder press. The exercises for the lower limbs will be free squats, lateral lunges, stepping hip thrusts, and plantar flexions, and participants will perform the training in the same manner as the HBG. The loads from all training sessions of the FxF group patients will be recorded, with patients being encouraged to reach concentric failure (ie, the inability to perform one more repetition) in the last series, as prescribed. We chose to prescribe training using maximum repetitions, where the number of repetitions to be performed is fixed and load variations occur based on this reference. A progressive increase in the load level will be initiated when the patient correctly performs the exercises with an ideal movement pattern for 2 consecutive days. Figure 2 presents an illustration of the resistance exercises.

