### Statistical Methodology

#### Sample Size Calculation

The G*Power 3.1 (Heinrich-Heine-Universität Düsseldorf) program was used to determine the sample size. The calculation was based on the HADS total score, which is defined as the primary outcome of the study, assuming a repeated-measures design with 3 groups (home-based, face-to-face, and control) and 3 assessment time points (baseline, postintervention, and 4-week follow-up). Considering an α level of .05 and power of .80, an effect size of *f* of 0.25 (moderate) was assumed for the group × time interaction, with an assumed correlation among repeated measures of 0.50 and a nonsphericity correction (ε) of 1.0. Under these assumptions, a sample of at least 42 participants, randomized into the 3 groups, is required. This sample size was calculated to detect differences between groups and was not designed to formally demonstrate equivalence between the interventions. Anticipating a dropout rate of approximately 30% (18/60), a total of 60 participants will be recruited to ensure the necessary final sample size of 42 participants.

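### The fixed, published block size of 6 lets up to one in five allocations be deduced by anyone who has seen all earlier ones, and opening envelopes after baseline does not prevent this

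*Protocol article*

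**What the plan says.** Under Randomization and Blinding, the Protocol article sets the ratio, "Participants will be randomly assigned in a 1:1:1 ratio to the HBG, FxF, or CG groups", and generates the sequence "with fixed block sizes of 6 to ensure balanced group allocation throughout recruitment". There is a single list, because "Stratification applies only to the recruitment process and not to the randomization procedure".

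The same section describes three protections:
- An independent researcher, with no part in recruitment, assessment or delivery, prepares sequentially numbered opaque sealed envelopes.
- Each envelope stays closed until baseline assessment is finished. The article credits this timing with keeping both allocation prediction and selection bias to a minimum.
- The researcher who handles recruitment, eligibility and evaluation is to be kept unaware of group membership.

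For delivery staff, however, "it will not be possible to blind the physical education professionals and physiotherapists responsible for the intervention". The Face-to-Face Program section adds: "Two researchers with experience in interventions for individuals with obesity will conduct the training sessions". These sessions are at the university's physiotherapy clinic, and the Participants section places data collection at the same university. Under Sample Size Calculation, "a total of 60 participants will be recruited to ensure the necessary final sample size of 42 participants".

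**The concern.** When every block has the same known length, the end of each block can be worked out from its beginning. A sealed envelope protects the allocation inside it. It does not protect against someone who has counted the previous allocations. Crediting the timing of envelope opening with minimizing prediction therefore claims more than that step can do.

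Arm membership is visible to part of the study team. Therapists deliver the exercise arms unblinded, the research team receives completion messages from home-based participants, and controls are contacted weekly. The article does not say whether the same therapists serve both exercise arms, which role contacts controls, or who opens the envelopes.

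If a prediction reached the person who books participants, there would be room to act on it. Recruitment works to income and rural quotas checked by telephone, and some exclusion criteria need clinical judgement. The Discussion itself notes that face-to-face attendance is harder for people who live remotely or have fewer means. Well-meant timing of a booking could then make the arms differ in who enters them.

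**Working it through.** **Inputs (all from the Protocol article).** Block size 6, fixed; three arms at 1:1:1, so two places per arm per block; no randomization strata, so one list; 60 participants.

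**The plan's own figure.** 42 / (1 − 0.30) = 60, which reproduces the stated total. 60 / 6 = 10 complete blocks. The article gives no figure for predictability.

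**Step 1: possible blocks.** 6! / (2! × 2! × 2!) = 720 / 8 = 90, all equally likely.

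**Step 2: places known with certainty, full observer.** This observer knows every earlier allocation in order and where each block starts.
- Places 1 to 4 are never certain.
- Place 5 is certain only when the last two places belong to the same arm: 3 × 4! / (2! × 2!) = 18 blocks, and 18 / 90 = 1/5.
- Place 6 is always certain.

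Expected share = (1/5 + 1) / 6 = 1.2 / 6 = 0.20. Over ten blocks, 10 × 1.2 = 12 of 60.

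**Step 3: partial knowledge, same observer.** The chance that at least one arm can be ruled out at places 1 to 6 is 0, 0, 1/5, 3/5, 1 and 1. The sum is 2.8, and 2.8 / 6 = 46.7%. Guessing the likeliest arm each time succeeds at 1/3, 2/5, 1/2, 8/15, 3/5 and 1. The sum is 3.367, and 3.367 / 6 = 56.1%.

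**Step 4: dependence on what is seen.** For an observer of one arm only, place 5 is certain when both of that arm's places are still unfilled after four (1/15). Place 6 is certain when one is still unfilled after five (1/3). (1/15 + 1/3) / 6 = 0.4 / 6 = 6.7%, or 4 of 60.

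| Observer | Certain | Of 60 | Best guess right |
|---|---|---|---|
| Sees all three arms, in order | 20.0% | 12 | 56.1% |
| Sees one arm | 6.7% | 4 | 46.7% |
| Sees no allocations | 0% | 0 | 33.3% |

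**Step 5: effect of varying the block size.** Lists of 60 were simulated (1,500 per setting) with block sizes drawn with equal probability. The observer saw every past allocation and knew the set of possible sizes, but not the size of the current block. As a check, the simulation returned 19.97% certain for fixed blocks of 6, against the exact 20%.

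| Block sizes | Certain | Best guess right |
|---|---|---|
| 6 (exact) | 20.0% | 56.1% |
| 3, 6, 9 | 3.7% | 55.1% |
| 6, 9 | 5.0% | 53.9% |
| 3, 6 | 8.7% | 57.5% |

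Varying the size removes most of the certainty but hardly changes best-guess accuracy.

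**The case against.** The strongest reply is that selection bias needs the person who enrols to be able to predict, and the article separates that person from delivery. The recruiter and evaluator is stated to be unaware of allocation, the envelopes come from someone outside recruitment, and therapists are not described as recruiting. Candidates also come through many channels and need a surgeon's signed indication, which limits discretion. Fixed blocks with concealed envelopes are a legitimate design choice. All of this stands, and it is why the concern is conditional.

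A reader might infer that one in five allocations will in fact be known to those who enrol. The documents do not support that: 20% requires someone who tracks all three arms in order. The one staffing number given, two researchers for face-to-face sessions, describes a view of one arm. Nor does it show that the whole team is small.

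A reader might also infer that selection would pass straight into the contrasts on the Hospital Anxiety and Depression Scale (HADS) because the scale is self-reported by unblinded participants. That merges two biases. Expectation effects do not depend on block size, and the Discussion already acknowledges them. Selection would act through differences at entry; HADS is measured before the envelope is opened, and baseline enters the mixed model as a repeated measure.

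Lastly, 56% best-guess accuracy against 33% by chance is no argument for varying the blocks, since it remains about 55% afterwards.

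What the reply does not answer is that opening envelopes late cannot prevent deduction from earlier allocations.

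**Conclusion.** The point holds as a modest weakness. Up to 12 of 60 allocations (20%) could be deduced from earlier ones. The range runs from 0% for a recruiter who sees none, through 6.7% for someone who sees one arm, to 20% for someone who sees everything in order and knows the block boundaries. These shares are exact given fixed blocks of 6 at 1:1:1 in one list of 60.

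Whether any bias follows depends on allocations leaking from delivery staff to the recruiter. That is possible where unblinded therapists and assessment share one university, but the documents do not show it. What the article does state too strongly is that the timing of envelope opening minimizes prediction.

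**What to change.** Before recruitment, or for the unused part of the list if enrolment has begun:
- Regenerate the sequence with randomly varying block sizes in multiples of 3, for example 3, 6 and 9.
- Withhold the sizes from study staff and public documents until enrolment closes.
- Reword the concealment sentence so that late opening is credited only with hiding the current allocation. Protection against prediction should rest on the undisclosed block sizes and on keeping the recruiter unaware of past allocations.

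This cuts fully determined allocations from 20% to about 3.7% (0.037 × 60 ≈ 2 of 60) for an observer who sees everything and knows the possible sizes.

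The cost is a regenerated list, a new set of envelopes and one revised sentence, with no extra participants. Recruitment may stop partway through a block. Since a block of 9 holds three places per arm, the final difference between any two arms could then be at most 3 participants.
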